**a.   Consent**

Participants who clicked on the experiment link were then taken to the consent page, which asked for the participant’s age to determine eligibility. Although being able to speak Odia was an inclusion criterion, we did not need to ask about their language abilities because the questionnaire was conducted in Odia. If they did not meet the eligibility criteria, they were thanked and dismissed. In the consent form, the structure of the questionnaire and topics were outlined before each section. Additionally, participants were reminded that the questionnaire was voluntary and that they would receive a compensation of ₹200 (Indian Rupees) via google pay or phonePe, both digital wallets.

**b.   Pre-exposure questions**

We started the survey by asking the respondents about their age, gender and their vaccination status. Participants who indicated that they had not received a COVID-19 vaccine were asked what their primary reason was for refraining from getting the particular vaccine. In an effort to understand attitudes and beliefs about COVID-19 vaccines (including vaccine hesitation towards COVID-19), participants were asked to rate their agreement on a series of statements adapted from Quinn
*et al*. (2019) on a five-point Likert scale from “strongly disagree” to “strongly agree”
^
10
^. Additionally, we asked how often and how likely specific COVID-19 thoughts had entered their minds in the last three months including the likelihood of contracting COVID-19 and the frequency that they thought about COVID-19 vaccinations. Finally, we included 13 questions about collectivism and individualism from Singelis
*et al*.’s 1995 vertical and horizontal collectivism and individualism scale
^
42
^. The three statements of each type of collectivism/individualism with the highest factor loadings along with one very culturally appropriate statement about family was included in the questionnaire.

**c.   Video randomization**

Subsequently, respondents were randomized to view one of the eight videos that were identically shot and edited with the exception of the independent test variables. The eight videos were categorized as follows:

· Female/Collective and Humorous,

· Female/Collective and non-humorous,

· Female/Individual and Non-humorous,

· Female/Individual and Humorous,

· Male/ Collective and humorous,

· Male/Collective and Non-humorous,

· Male/Individual and Humorous,

· Male/Individual and Non-humorous.

 After, watching the videos participants were asked how many times they had watched the videos and the duration for which they watched the video to assess whether they had completed watching the video.

**d.   Post-exposure questions**

After being randomized to view one of the videos, participants were asked about their reactions, including the extent to which they found the video to be important, or relevant or caused them to reflect about the COVID-19 vaccine. Participants were also asked about the tone of the video as a manipulation check to gauge whether the humorous videos were perceived as humorous, whether the collectivistically oriented videos were perceived as such, and the extent to which viewers correctly remembered the protagonist gender. We also asked questions about the characters in the video to assess recollection. This included items on source credibility adapted from McCroskey & Teven (1999)
^
76
^. Lastly, we collected information about participants’ social media use, followed by their general demographic information.

**
*Qualitative component*
**

Qualitative research will focus on eliciting the reactions from vaccine-hesitant individuals, identified through the online survey. Our local partners at D-COR will conduct 12 online focus groups, to discuss participant's beliefs and reactions to the videos. Focus groups will be stratified by both age and gender. Of the pool of participants who agree to participate in the qualitative work, eligibility will be decided based on their age and gender (to get a sound distribution of age and gender groups). Focus groups will run for 90 minutes and be conducted in Odia. In the first half of the focus group, moderators will guide discussion around beliefs and attitudes around vaccines – both COVID-19 and vaccines in general – and invite participants to share their concerns. In the second half of the focus groups, participants will be invited to share their reactions to the videos.

 We also plan to conduct up to 20 semi-structured interviews with individuals who may prefer the one-on-one format. This also provides more flexibility for the research team to delve deeper into any emergent themes that may arise during focus groups.

**
*Social media analysis component.*
**

Two diametric vaccine videos will be posted on YouTube and promoted through social media channels, including Facebook and WhatsApp. Engagement with videos will be tracked through YouTube analytic metrics. All public comments posted under the videos in English, translated from Odia when required will be analyzed for recurring keywords, emerging themes, and sentiment, using tools from YouTube Data Tools, TextBlob and Vadar on Communalytic. Additionally, social network analysis to visualize the comment network for each video as well as the broader channel network to assess engagement across all videos will be conducted. Gephi software will be used to construct networks, with measures including the number of nodes (individuals), edges (connections between nodes), degrees (measure of interaction), and modularity (measure of communities within the network).

## Measurement

### Statistical analysis and power calculation

**Online experiment component:** We assumed that, prior to exposure, 30% of the population would be vaccine-hesitant and that exposure would affect the attitudes of 10% of the viewers. To achieve power of 80%, with an alpha of 5%, the required sample size would be 294 per group, which we rounded up to 300. To be able to conduct sub-analyses along caste (three subgroups) and three age groups (i.e., nine groups in total), the overall required sample size was calculated to be 2,700. 

**Data analysis**. Data analysis will be done in two phases. First, we will conduct manipulation checks for the three variables that were manipulated. We manipulated the scripts to have either an individualistic or a collectivistic appeal. Responses to questions that asked about the extent to which the videos had an individualistic appeal (coded as 1) or a collectivistic appeal (coded as 5) will be subjected to a t-test in which the assignment to condition (individualistic or collectivistic) will be the independent variable. Similarly, the extent to which the videos were perceived to be humorous will also undergo a t-test. Finally, we will ask participants to recall whether the main protagonist was a male or female. This will be compared against the assignment variable (whether assigned to the male or female protagonist) through a chi-square test. If the results of the two t-tests and the chi-square test are significant, we will deem the manipulations to have been successful. Second, we will run an analysis of covariance (ANCOVA) model in which assignment to experimental conditions will be the three independent variables (individualistic or collectivistic appeal; humor or serious tone; and protagonist gender) and attitudes toward vaccines will be the dependent variable. In this model we will control for demographic indicators. We will also test for three two-way and one three-way interactions among the independent variables.

**Qualitative component:** From the survey respondents (
*n*=2,700), we will identify the 10% (
*n*=270) with greatest vaccine hesitancy, as determined through their pre-exposure scores on the vaccine confidence index. This subsample will be invited to participate in focus groups. From this pool, we will purposively select participants to fill up to 12 focus groups, each with 8 participants. To ensure we hear diverse viewpoints from different segments of the population, groups will be stratified by both age (18–22, 23–30, 31–45) and gender (male, female). Following this design, we expect a maximum of 100 participants (
Table 2).

**Table 2. T2:** Expected numbers and description of focus group (FG) participants.

	Male	Female	Total
Age 1: 18–22 years	2 FGs ( *n*=16)	2 FGs ( *n*=16)	4 FGs ( *n*=32)
Age 2: 23–30 years	2 FGs ( *n*=16)	2 FGs ( *n*=16)	4 FGs ( *n*=32)
Age 3: 31–45 years	2 FGs ( *n*=16)	2 FGs ( *n*=16)	4 FGs ( *n*=32)
Total	6 FGs ( *n* =48)	6 FGs ( *n* =48)	12 FGs ( *n*= 96)

Additionally, time and resources have been allocated to conduct semi-structured online interviews with up to 20 additional people to delve deeper on any emergent topics that may arise over the course of the study. This would lead to a maximum of 120 participants in the qualitative portion of the study.

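### The 80% power is calculated for the effect of watching a video, so it does not apply to the planned comparisons between videos

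*Protocol article*

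**What the plan says.** The sizing is in the protocol article under Statistical analysis and power calculation. It starts from a hesitancy rate and an effect of exposure: "We assumed that, prior to exposure, 30% of the population would be vaccine-hesitant and that exposure would affect the attitudes of 10% of the viewers". For 80% power at a 5% alpha, "the required sample size would be 294 per group, which we rounded up to 300". The total is then built from sub-analyses in three caste groups by three age groups: "i.e., nine groups in total), the overall required sample size was calculated to be 2,700".

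The data analysis paragraph that follows has two phases. The first is manipulation checks. The second is an ANCOVA with attitudes toward vaccines as the dependent variable, the three manipulated factors as independent variables, and demographic indicators as controls. It adds: "We will also test for three two-way and one three-way interactions among the independent variables". It describes no before-versus-after test and no test of a hesitancy proportion.

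On allocation, the Video randomization section says that "respondents were randomized to view one of the eight videos". No arm goes without a video. Study design adds that attitudes, beliefs and intentions are collected before and after viewing. The Abstract's primary research question covers the three factors both singly and in combination. The section on the online experiment reports 2,349 responses.

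**The concern.** A power statement describes one contrast on one outcome. Here the contrast in the sizing is no exposure against exposure, on a rate. The contrasts in the analysis are one kind of video against another, among people who are all exposed, on an attitude measure suited to ANCOVA (the pre-exposure attitude items are five-point Likert items). No expected difference between video types, no SD and no interaction size is given.

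At stake is how the results will be read. A reader who sees 80% power beside a question about separate and combined effects will assume that it covers that question. A null interaction could then be reported as fairly good evidence that the factors do not act together, although the calculation says nothing about that.

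**Working it through.** **Inputs.** From the power paragraph: 30% hesitant before exposure, an effect on 10% of viewers, 80% power, alpha 5%, 294 per group rounded to 300, and nine subgroups. From Study design and Video randomization: eight arms, all exposed. From the online experiment section: 2,349 responses. Two-sided testing is not stated; it is the reading that reproduces the figure. Normal quantiles are 1.960 and 0.842, which sum to 2.802.

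**1. Reproducing 294.** Two independent proportions, 0.30 and 0.20, pooled variance:

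n = [1.960·√(2·0.25·0.75) + 0.842·√(0.30·0.70 + 0.20·0.80)]² / 0.10² = (1.200 + 0.512)² / 0.01 = 293.2, so 294.

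Other readings do not give 294: one-sided 231, unpooled 291, arcsine 292, continuity-corrected 313, 30% vs 40% 356, 30% vs 27% 3,554. The arithmetic is correct, and 9 × 300 = 2,700.

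**2. Does that contrast occur in the ANCOVA?** Suppose every video lowers hesitancy from 30% to 20% and shifts attitudes equally. The sizing assumption is then fully met. All eight arm means are equal, so three main effects, three two-way interactions and the three-way interaction are all zero. The 80% does not carry over to any of the seven.

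**3. Does it fit a before-versus-after reading?** The same people answer twice, so the matching calculation is McNemar. With discordant share s and net change d = 0.10:

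n = [1.960·√s + 0.842·√(s − d²)]² / d²

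- s = 10%: 76.1, so 77
- s = 20%: 154.6, so 155
- s = 30%: 233.1, so 234
- s = 38%: 295.9, so 296

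The last row is what independence gives (0.30·0.80 + 0.70·0.20 = 0.38). The independent-groups figure therefore matches only if the two answers are unrelated. With less discordance, 294 is more than needed.

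**4. What the ANCOVA can detect.** Equal arms, SD = 1, no covariate gain, 80% power, two-sided 5%. A main effect compares halves of the sample, with standard error 2/√N. The two-way interaction is a difference of differences (4/√N). The three-way contrast is the difference between two such differences (8/√N). One video against another has √(2/(N/8)) = 4/√N. Multiplying by 2.802:

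| Contrast | N = 2,700 | N = 2,349 |
|---|---|---|
| Main effect | 0.11 SD | 0.12 SD |
| Two-way interaction | 0.22 SD | 0.23 SD |
| Three-way contrast | 0.43 SD | 0.46 SD |
| One video vs another | 0.22 SD | 0.23 SD |

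**5. Power under assumed differences in hesitancy after viewing.** The documents give no difference between videos, so these are assumptions shown as a range. At N = 2,349, the arms hold 2,349/8 = 293.6 people and the factor levels 1,174.5.

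- Two videos: 30% power for 25% vs 20%; 80% for 30% vs 20%.
- Main effect: 23% power for 21% vs 19%; 83% for 25% vs 20%; above 99.9% for 30% vs 20%.

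**The case against.** The strongest reply is that the calculation serves a different aim. The Abstract's objective is whether videos can change attitudes, these are measured before and after viewing, and 300 is attached to each caste-by-age subgroup. On that reading 294 is a conservative size for a pre/post change in each subgroup, and the test may be specified in a plan that is not shown. This stands in part. Step 3 does not exclude the reading, and it would go too far to say that the 80% can belong to no comparison at all. It does not rescue the ANCOVA, which is the outcome analysis that the article describes.

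A reader might also infer that differences between versions must be smaller than the whole exposure effect. The documents do not support that. Role of humor allows that humour may weaken intentions to act. If one version works and its counterpart is inert, the split after viewing is 20% vs 30%, and two videos at about 294 per arm then have 80% power. If one backfires, the gap is wider.

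A third point concerns coding. With balanced ±1 codes all seven terms have the same standard error. The larger interaction figures in step 4 apply to differences of differences, and that convention must be stated with them.

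Finally, data collection took place in February 2022, so the sample size cannot change. That is true, but the analysis is still described in the future tense and the power claim can be corrected.

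**Conclusion.** The point holds as a mismatch between the target of the sizing and the described analysis. It is not an arithmetic error, since 294 reproduces exactly. The 80% applies to none of the seven ANCOVA effects, including those that answer the joint part of the primary question.

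A reader might conclude that the trial is underpowered. The documents do not show that: main effects of about 0.11 to 0.12 SD are detectable with 80% power. Interactions need to be two to four times as large on the difference-of-differences scale, and no document says what size is expected.

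The conclusion rests on reading 10% as percentage points and hesitancy as yes/no (both supported by the exact match to 294), on treating attitudes as a score (from the ANCOVA and the Likert items), on equal arms, and on no gain from covariates. The article names only demographic covariates, and their gain cannot be worked out from it. It also treats all 2,349 responses as analysable, which the article does not confirm.

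**What to change.** Revise the power paragraph as follows.

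- Keep the stated basis on record: 30% vs 20%, 294 rounded to 300, nine subgroups, 2,700. Say that the 80% power does not refer to the ANCOVA.
- Add the minimum detectable effects from the table in step 4, with the contrast definitions, labelled as computed after the sample was fixed. Use the analysable N if it is below 2,349.
- Say that a null interaction or a null comparison of two videos must not be read as a result obtained with 80% power.
- Give any power for an assumed difference over a range, such as 30% for 25% vs 20% and 80% for 30% vs 20% between two videos.
- If the 294 was meant for a before-versus-after comparison, name that comparison and its paired test.
- Do not write that the trial was sized for main effects. The 2,700 comes from the subgroups.

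The cost is one rewritten paragraph, with no change to design, data or model. The article's claim for joint effects becomes less favourable.

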### Study setting

This research was conducted in the eastern Indian state of Odisha, with a population of about 46 million people
^
64
^. In 2011, 83.3% of the state lived in rural areas, and 16.7% of the population lived in urban areas
^
65
^. Additionally, 40% of the state’s population belong to Scheduled Tribes (22.85%) or Scheduled Castes (17.13%)
^
65
^. Odisha is also a state with relatively high levels of childhood immunization. Between 2019 and 2021, 91% of children between 12–23 months received all basic vaccinations against tuberculosis, diphtheria, pertussis, tetanus, polio, and measles and 98% of children between 12–23 months were at least partially vaccinated against the six major childhood illnesses
^
64
^. 

There have been 1 million confirmed cases and 8,400 deaths reported since the start of the COVID-19 pandemic in Odisha
^
66
^. Vaccine distribution in the country is decentralized, with each Indian state responsible for local administration and vaccination rates vary widely by state
^
67
^. As of February 2022, 95% of individuals over the age of 18 years had received the first dose, 92% were eligible for a second dose, and 80.3% of all eligible individuals had received both doses, making vaccination rates in Odisha higher than the national average (Express News Service, 2022). 

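### The total of 2,700 gives each of the nine caste-by-age cells half the sample that a two-group comparison inside it needs, so power for a factor contrast in an equal cell is about 52%, not 80%

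*Protocol article*

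**What the plan says.** The sizing is in the protocol article under Statistical analysis and power calculation (online experiment component). It assumes that "prior to exposure, 30% of the population would be vaccine-hesitant" and that "exposure would affect the attitudes of 10% of the viewers". With 80% power and 5% alpha, "the required sample size would be 294 per group, which we rounded up to 300". The paragraph then continues: "To be able to conduct sub-analyses along caste (three subgroups) and three age groups (i.e., nine groups in total), the overall required sample size" is put at 2,700. It does not say which two groups the 294 compares.

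The same section plans an ANCOVA of vaccine attitudes. Its independent variables are the three randomised two-level factors (appeal, tone, protagonist gender), with adjustment for demographics and tests of the interactions among the factors. The Study design section describes a 2 x 2 x 2 between-subjects experiment with eight videos and with attitudes recorded before and after viewing. The Evaluation of videos section reports 2,349 responses.

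**The concern.** A sample size per group is the number in each side of a comparison. The nine groups by which the plan multiplies are not sides of a comparison. They are subgroups, and a comparison is to be made inside each. A cell of 300 therefore has to be divided between the two levels of whichever factor is being tested.

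The plan presents 2,700 as the number needed for these sub-analyses. A reader would take it that a null result in, say, one caste and age group comes from an analysis with 80% power. If power is near 50%, such a null says little. A significant cell result would also tend to overstate the effect, because at low power only large estimates reach significance.

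**Working it through.** **Inputs.** From Statistical analysis and power calculation: 30% hesitant, a 10% effect, 80% power, 5% alpha, 294 rounded to 300, nine cells, total 2,700. From Study design: eight videos, between-subjects. From Evaluation of videos: 2,349 responses. Assumptions: a two-sided test (sidedness is not stated), equal allocation to videos, and equal cells.

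**1. Reproducing 294.** Two independent proportions, p1 = 0.30, p2 = 0.20, mean 0.25, pooled variance under the null, no continuity correction:

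n per group = [1.960 x sqrt(2 x 0.25 x 0.75) + 0.8416 x sqrt(0.30 x 0.70 + 0.20 x 0.80)]² / 0.10²
= [1.2002 + 0.5119]² / 0.01 = 293.15, so 294.

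The match is exact. Other readings miss it: 30% versus 40% gives 356, a relative 10% (30% versus 27%) gives 3,554, and a one-sided test of 30% versus 20% gives 231. So 294 is the size of each of two groups, and one comparison needs 2 x 294 = 588.

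**2. What 2,700 supplies.** 9 x 300 = 2,700, which is 300 people per cell and 150 per level of a factor. Two full groups in each of nine cells would take 9 x 588 = 5,292 (5,400 with the rounded 300).

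**3. Power on the same basis.** With n per level,

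power = Φ[(0.10 x sqrt(n) − 1.2002) / 0.6083].

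| Comparison (30% vs 20%) | n per level | Power |
|---|---|---|
| Size stated in the plan | 300 | 80.9% |
| Factor contrast, equal cell, N = 2,700 | 150 | 51.6% |
| Factor contrast, equal cell, N = 2,349 (2,349 / 9 / 2) | 130.5 | 46.2% |
| One-way subgroup of 900, N = 2,700 | 450 | 93.5% |
| Whole-sample factor contrast, N = 2,349 | 1,174.5 | over 99.9% |

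With 150 per level, 80% power is reached only for a fall from 30% to about 16%, roughly 14 points instead of 10.

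**4. The pre/post alternative.** Suppose the 300 people in a cell are each tested before and after, and the two measurements are independent. The discordant shares are 0.30 x 0.80 = 0.24 and 0.70 x 0.20 = 0.14. A McNemar test then needs [1.960 x sqrt(0.38) + 0.8416 x sqrt(0.38 − 0.01)]² / 0.01 = 295.9, so 296, and 300 people give 80.5%. Positive correlation raises that.

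**5. Interaction tests, for use in the fix.** Take N = 2,349 and equal age thirds (391.5 per level), with a 10-point effect in one third and none in another. The standard error of the difference in differences is sqrt[(0.21 + 0.16 + 0.21 + 0.21) / 391.5] = 0.0449. Power is Φ(0.10 / 0.0449 − 1.960), about 60%.

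**The case against.** The strongest reply is that the inputs describe a change from before to after exposure, that every arm sees a vaccine video, and that attitudes were measured twice. On that reading 300 per cell is enough (step 4), and the paragraph does not say that the sub-analyses use the ANCOVA. This stands as far as it goes: the plan leaves the compared groups unnamed, and one reading makes the number adequate. It does not rescue the plan. The design, the only model specified for the experiment's outcome and the primary question all concern contrasts between randomised factors. A before-after change inside a cell has no unexposed comparator and cannot separate appeal, tone or gender. If it was the basis, the section sizes an analysis that it does not specify.

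A second reply is that 52% is a two-proportion figure while the planned outcome is an attitude analysed by ANCOVA. That is correct. The figure restates the plan's own sizing claim and does not predict the power of the ANCOVA, for which the article gives no standard deviation.

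Two stronger readings are tempting and should not be drawn. A reader might infer that half the sample means half the power. It does not: 51.6 / 80 is about 65%, and 46.2 / 80 about 58%. A reader might also apply the state shares in Study setting, where 40% of people "belong to Scheduled Tribes (22.85%) or Scheduled Castes (17.13"%), and quote a specific low power for those cells. The article does not define its three caste subgroups, and the shares are for the whole state, not for 18- to 35-year-olds recruited by link. All that follows is that cells smaller than average have less power than the equal-cell figure.

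**Conclusion.** The point holds for the nine crossed cells. By the plan's own inputs each cell holds 300 people where a two-group comparison needs 588. Power for a two-level factor contrast is about 52% at 2,700 and about 46% at 2,349, against 80% stated. This rests on a between-subjects reading of the sub-analyses, the binary 30% versus 20% basis, a two-sided 5% test, equal allocation and equal cells.

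The reach is limited. Main effects in the whole sample are not touched, and caste alone or age alone remains well powered for a within-subgroup contrast if the groups are of similar size. What is wrong is the stated justification for 2,700 and the confidence it lends to cell-level results.

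**What to change.** - State which contrast the 294 per group refers to.
- Withdraw the statement that 2,700 is the size required for the nine crossed sub-analyses. Give instead about 46% to 52% power per equal cell, labelled as a two-proportion figure for 30% versus 20%, and note that smaller cells have less.
- Examine caste and age one at a time, through factor-by-caste and factor-by-age interaction terms in the whole-sample ANCOVA, labelled exploratory.
- Do not attach within-subgroup power to those interaction tests. A single age third at N = 2,349 has about 90% for a contrast inside it (391.5 per level). The test of one third against another has only about 60% if the 10-point effect is confined to one of them.

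The cost is a reworded sample-size paragraph and subgroup plan, and a less favourable stated subgroup power. No new participants are needed.

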## Abstract

**Background:** Vaccine hesitancy is one of the greatest challenges to the success of coronavirus disease 2019 (COVID-19) vaccination campaigns. Videos promoting vaccines have a narrow scope focusing solely on facts, and less on the emotional and narrative elements of communication that can be equally persuasive. The role of humor, for example, has remained largely unexplored.

**Objective:** This study investigates whether theory-based videos can change people’s attitudes, beliefs, and intentions to receive the second COVID-19 vaccine. Our primary research question is: How do collectivistic and individualistic appeals, humor, and protagonist gender individually and jointly affect vaccination attitudes, beliefs, and intentions?

**Methods:** This project tapped into the underutilized Indian film industry—the world’s largest film producer—to promote vaccination messaging through short videos. Feedback from a community advisory board was utilized to inform the video scripts that were then shot by a production team. Eight videos were filmed and shared by adopting a 2 (appeal: individualistic or collectivistic) x 2 (tone: humor or non-humor) x 2 (protagonist gender: male or female) between-subjects design approach. Our sample includes Odia-speaking participants aged between 18 – 35 years old randomly assigned to watch one of the eight study videos. An online survey questionnaire, social media network analysis, and small group qualitative interviews will be utilized to explore how the entertainment-education videos can be used to reduce vaccine hesitancy.

**Discussion:** Vaccine messages do not fall into a cultural or cognitive vacuum. People process and make sense of information based on their prior experience, properties of the message, and their social environment. Yet, these considerations have taken secondary importance in vaccine communications. This research shows that it is possible to deliver high-caliber videos created in accordance with the audience's cultural and cognitive background.

**Conclusions: **This study will inform future health promotion messaging through brief videos on the internet.

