### Study design

An online experiment was conducted through a 2 (appeal: individualistic or collectivistic) x 2 (tone: humor or non-humor) x 2 (protagonist gender: male or female) between-subjects design. Participants were recruited through a link posted on the Swasthya Plus Network (SPN) Odia website, and was shared by SPN on their public Odia WhatsApp channels. In order to be eligible for the study, participants needed to be between the ages of 18–35, and speak Odia. We did not check for language ability as the recruitment pages, channel, survey, and videos were all in Odia. Odia-speaking participants (N = 2,700) between the ages of 18–35 years were randomly assigned to watch one of the eight study videos, providing their vaccination attitudes, beliefs, and intentions both before and after viewing the videos. We tested for main effects of appeal, tone, and protagonist gender (as well as the underlying two-way and three-way interactions). During script development, we also sought the feedback from a community advisory board for cultural appropriateness. Videos were shot in December 2021 and the experiment itself was launched in January 2022.

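### The primary question asks about attitudes, beliefs and intentions, but the only effect model is for attitudes, so intention has no planned analysis and the place of beliefs is unclear

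*Protocol article*

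**What the plan says.** The Abstract of the protocol article sets the objective as finding out whether the videos "can change people’s attitudes, beliefs, and intentions to receive the second COVID-19 vaccine". Its primary research question asks how the three message features "individually and jointly affect vaccination attitudes, beliefs, and intentions".

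The Study design section describes participants as "providing their vaccination attitudes, beliefs, and intentions both before and after viewing the videos". The next sentence reads: "We tested for main effects of appeal, tone, and protagonist gender (as well as the underlying two-way and three-way interactions". It names no outcome.

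Under Statistical analysis and power calculation the article states: "Data analysis will be done in two phases". The first phase is manipulation checks (two t-tests and a chi-square test). For the second it says: "Second, we will run an analysis of covariance (ANCOVA) model". The three assigned factors are the independent variables, demographic indicators are controlled for, and "attitudes toward vaccines will be the dependent variable". It adds: "We will also test for three two-way and one three-way interactions among the independent variables". The power assumption in the same section is also stated on attitudes.

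**The concern.** The question names three outcomes and the effect model names one. This is more than detail left to a fuller plan, because the article does state the dependent variable and that variable does not match its own primary question.

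Intention matters most here. The Introduction motivates the study by the people who had a first dose but not a second, and the objective follows from that. A result on attitudes does not by itself show an effect on intention to take that dose. Followed as written, the analysis would report on attitudes and leave the second-dose question open. If intention were added later, there would be no stated ranking of the outcomes and no rule for the extra tests.

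**Working it through.** **The plan's own figure.** The article gives 294 per group for 80% power and 5% alpha, from 30% hesitant before exposure and a 10% effect on attitudes. Reading this as 30% against 20%, two-sided, with pooled variance and no continuity correction:

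n = [1.960 × √(2 × 0.25 × 0.75) + 0.842 × √(0.30 × 0.70 + 0.20 × 0.80)]² / 0.10²

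= [1.960 × 0.612 + 0.842 × 0.608]² / 0.01 ≈ 293.2, rounded up to 294.

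The figure reproduces. It bears on this point in one way only: the effect that sized the study is an effect on attitudes. No effect on intention is assumed anywhere.

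**The three outcomes, place by place.**

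| | Attitudes | Beliefs | Intentions |
|---|---|---|---|
| Objective and primary question (Abstract) | named | named | named; the objective ties it to the second dose |
| Said to be collected before and after (Study design) | yes | yes | yes |
| Pre-exposure questions | one Likert series, shared with beliefs | same series | no item listed |
| Post-exposure questions | not listed | not listed | not listed |
| Power assumption | yes | not named | not named |
| Dependent variable of the ANCOVA | yes | not named | not named |

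**Attitudes** are covered by the model.

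**Intentions** appear in the question and among the data said to be collected, but in no model, test or effect measure. The manipulation checks do not fill the gap, since they concern how the video was perceived.

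**Beliefs** cannot be placed. The pre-exposure section describes a single set of agreement statements meant to capture attitudes and beliefs together. If that set yields one score, the attitude outcome already includes beliefs. If it yields two, beliefs have no model. The article does not say which.

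**Whether another component answers the question.** The focus groups discuss beliefs among the most hesitant respondents but do not compare the randomized conditions. The social media work uses two videos that differ on all three factors at once, so it cannot separate their effects.

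**Number of tests.** Each factorial model has 3 main effects + 3 two-way interactions + 1 three-way interaction = 7 effects. A model for intention brings the count to 14, and a separate model for beliefs to 21. A repair therefore needs a rule for the added tests.

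**Whether the data exist.** The Study design section says intention was measured at both times, yet neither the pre-exposure nor the post-exposure list mentions an intention item. The questionnaire is in extended data that are not shown. The two accounts do not agree, and the article alone cannot settle which is complete.

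**The case against.** The best defence is that attitudes is used as an umbrella term. The survey treats attitudes and beliefs as one series, and the sentence on main effects and interactions directly follows the one naming all three outcomes. A condensed article may also leave secondary models to a fuller plan.

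Part of this stands. A reader might infer that two of the three outcomes have no planned analysis. The article does not support that, because beliefs may be inside the attitude score. The defence does not reach intention. The article lists intention separately each time it names the outcomes, the sentence on main effects and interactions names no outcome, and the analysis section names attitudes alone. A fuller plan could add a model, but this text would still disagree with itself.

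A reader might also try to size the harm in one of three ways, and the article supports none of them:

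- **Carrying an attitude effect over to intention through an assumed correlation.** The article gives neither value, and the method assumes the videos act on intention only through attitudes.
- **Estimating how many participants lack a second dose from the statewide coverage figures.** Those figures describe all adults in Odisha, whereas the sample is people aged 18–35 recruited online.
- **Quoting a false-positive rate for all three outcomes as if the tests were independent.** Outcomes of this kind are likely to be correlated, and the article does not plan those tests.

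Finally, a ranking of outcomes written now comes after data collection. That is a fair limit on any repair, and the fix has to acknowledge it.

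**Conclusion.** The concern holds for intention and is undecided for beliefs. One of the three outcomes in the primary question has a stated model, one has none, and one depends on a scoring rule that the article does not give. This rests on the text alone and needs no assumed effect size or error rate.

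The randomization and the data are unaffected. The point should be corrected because the analysis as written does not answer the part of the question about second-dose intention. Whether it can be answered depends on intention having been measured, which the article asserts in one section and does not bear out in its lists of survey items.

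**What to change.** In Statistical analysis and power calculation:

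1. State whether the attitude score includes the belief items.
2. Add the same factorial ANCOVA for post-exposure intention, and for post-exposure beliefs if they are scored separately. Adjust each for its own pre-exposure value where that was measured.
3. Label these models secondary to attitudes, the outcome on which the power assumption is stated. Either give a multiplicity rule for the added tests (7 per model) or report the models as exploratory.
4. Report second-dose intention among participants without a second dose as a supporting analysis, using the vaccination status asked before exposure if it records the number of doses.
5. Reconcile the pre-exposure and post-exposure lists with the Study design section, so that it is clear which of the three outcomes was asked and when.
6. If intention was not measured or will not be analysed, narrow the objective and the primary question instead.
7. Date the change and state whether outcome data had been examined. The article reports 2,349 responses collected in February 2022, and the Study design section already describes the tests in the past tense.

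The cost is small if the Study design section is right about what was collected: one or two further models and some rewording, with no new data. Two limits remain. The supporting analysis will be less precise because it uses fewer participants, and a ranking set after data collection carries less weight than one set before.
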